### Area-Level Health Data

Community-level vaccination coverage and healthcare utilization outcomes will be analyzed longitudinally as clusters transition from control to intervention conditions. Mixed-effects models will adjust for time effects and clustering to estimate intervention-associated differences while accounting for the stepped-wedge rollout. Zip code–level indicators will be incorporated to assess potential geographic crossover between clusters.

Exploratory analyses will examine area-level influenza-like illness, hospitalizations, and emergency department utilization during the intervention period, recognizing limited statistical power for these outcomes.

### Exploratory Analyses

Exploratory subgroup analyses may be conducted to assess whether intervention effects vary by participant characteristics, including age, primary language, and baseline social media use. These analyses will be considered hypothesis-generating and interpreted cautiously.

### Interim Analyses

Interim analyses will be conducted at prespecified time points to summarize implementation metrics, engagement patterns, and participant feedback. These analyses will be used to monitor feasibility and fidelity of the intervention. Interim findings will inform operational adjustments (e.g., scheduling or delivery format) but will not be used to modify primary outcomes or determine early trial termination.

### Missing Data

Missing data may occur due to non-adherence or participant attrition over the course of the study. Multiple imputation by chained equations will be used to address missing survey data under the assumption that data are missing at random. Imputation models will incorporate demographic variables, baseline measures, cluster indicators, and time effects. Sensitivity analyses will be conducted to evaluate the robustness of findings to different assumptions about missingness. Results from imputed datasets will be compared with complete case analyses to assess the robustness of findings.

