## Methods

### Study Design

This study will use a non-randomized, stepped-wedge design to evaluate the implementation and effectiveness of the Dime La VerDAD intervention across community-based cohorts of promotores de salud. Promotores will be enrolled in clusters defined by the geographic areas in which they provide services. Three clusters will include promotores serving two geographically adjacent communities, and one cluster will include promotores serving a single, geographically distinct area. Each cluster will include approximately 5–14 promotores, depending on the number of communities represented, with larger clusters corresponding to areas serving multiple adjacent neighborhoods. This cluster structure was informed by pilot data indicating that promotores frequently serve multiple neighboring communities; grouping adjacent areas is intended to reduce contamination across study conditions and minimize spillover effects.

At six-month intervals, each cluster will transition from the control condition to the intervention, such that all clusters will receive the intervention by the end of the study period. During the control phase, promotores will continue their usual social media practices without structured training or guidance from the study team. Upon transition to the intervention phase, participants will complete a structured science communication curriculum and apply these principles by developing and sharing social media content within their networks.

Outcomes will be compared within clusters over time, with each cluster serving as its own control, and between clusters as sequential crossover to the intervention occurs. This design allows for both within-cluster and between-cluster comparisons while accounting for secular trends in social media use and vaccination-related attitudes.

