### Surveys

Surveys will be administered to promotores and members of their social media networks at multiple time points aligned with the stepped-wedge rollout.

At baseline, promotores will complete a 30-minute survey assessing demographics, social media use patterns, and confidence in applying science communication principles related to respiratory virus prevention [28]. The survey will capture social media platform use, including applications used, number of network members, and frequency of reading, posting, and sharing content, as well as experience addressing vaccine-related health claims. These data will be used to describe variability in social media practices, identify emerging platforms for inclusion in analyses, and characterize posting behaviors across community areas. Survey items will draw from the PhenX Toolkit [29], including modules on social determinants of health, COVID-19 exposure, technology access, and media use.

Promotores will also complete brief surveys immediately before and after the training to assess learning related to evaluating online health information, assessing source credibility, and developing evidence-based messages. Post-training surveys will also capture perceived usefulness, acceptability, and feasibility of the training. Implementation outputs will be documented by tracking completion of curriculum assignments and the number and characteristics of infographics and posts produced (e.g., inclusion of credible sources, use of narrative elements).

Additional follow-up surveys will be administered at study conclusion to assess perceived reach, communication experiences, and confidence in applying science communication strategies.

Members of promotores’ social media networks will complete surveys at baseline, at 6-months, and post-campaign to assess exposure to social media content, recall, perceived credibility, and vaccination-related decision-making.

Individuals who wish to receive compensation for completing the surveys will be asked to provide their email address. This contact information will not be stored with survey response data.

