### Surveys

Descriptive data will summarize participant characteristics, social media use patterns, and baseline measures using appropriate summary statistics. Categorical variables will be reported as counts and percentages, and sparse categories will be combined where appropriate. Continuous variables will be assessed for distributional assumptions and summarized as means with standard deviations or medians with interquartile ranges.

Changes in survey-based outcomes, including knowledge, confidence in applying science communication principles, and vaccination-related decision-making, will be evaluated using generalized linear mixed models (GLMMs). These models will account for clustering at the promotor and neighborhood levels and will include fixed effects for time and intervention status. Relevant demographic and contextual covariates (e.g., age, primary language, and zip code) will be included as appropriate.

Repeated measures analyses will be used to assess changes over time across baseline, 6-months, and post-campaign assessments. Binary outcomes will be analyzed using logistic mixed-effects models, while continuous and ordinal outcomes will be analyzed using linear or cumulative link mixed models, depending on distributional assumptions.

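### Survey data are expected to go missing through non-adherence, but the imputation predictors listed include no adherence measure, so missing at random is doubtful and the rollout effect may be biased in either direction

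*Protocol article*

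**What the plan says.** The Missing Data section of the protocol article opens with the expected causes: "Missing data may occur due to non-adherence or participant attrition over the course of the study". The method follows: "Multiple imputation by chained equations will be used to address missing survey data under the assumption that data are missing at random". The predictors are then listed: "Imputation models will incorporate demographic variables, baseline measures, cluster indicators, and time effects". Neither adherence nor intervention status is among them.

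Two robustness checks are planned. One is general: "Sensitivity analyses will be conducted to evaluate the robustness of findings to different assumptions about missingness". The other is concrete: "Results from imputed datasets will be compared with complete case analyses to assess the robustness of findings".

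Other sections bear on this:

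- Surveys (under Outcomes) shows that adherence is recorded: "Implementation outputs will be documented by tracking completion of curriculum assignments and the number and characteristics of infographics and posts produced". The Social Media Engagement analysis section also counts posts, as a fidelity measure.
- Table 1, Session 6, gives the promotor both tasks as homework: posting the finished content and, six months after the baseline focus group, inviting network members to the post-survey.
- Surveys (under Data Analysis) describes the outcome models: "These models will account for clustering at the promotor and neighborhood levels and will include fixed effects for time and intervention status". Member records must therefore be attributable to a promotor.
- Study Design gives the aim, which is to "evaluate the implementation and effectiveness of the Dime La VerDAD intervention across community-based cohorts of promotores de salud", and sets intervention status by the cluster's crossover.

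**The concern.** MAR is a statement about the variables in the imputation model. It can hold when missingness depends on adherence and adherence is conditioned on. It is doubtful when adherence also affects the outcome and is left out.

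That situation is plausible here. A promotor who stops posting gives the network less of the campaign and may also not send the follow-up invitation. Response and benefit would then fall together. Missing members of such networks would be imputed from observed members of the same cluster and period, most of whom belong to adherent promotores. The estimate would drift from the effect of rolling the programme out towards its effect where promotores carried it through.

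The outcome at stake is the primary one, vaccination-related decision-making among network members.

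**Working it through.** **Inputs from the protocol article (Sample Size).** Baseline 45%, relative risk 1.5, at least 35 promotores, about 45 members each, four clusters, within-participant correlation 0.25. The stated target reproduces: 0.45 × 1.5 = 0.675, reported as 68%. The planned effect is 68 − 45 = 23 points.

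**Assumptions (the documents give no rates).** A share s of intervention-phase members belongs to non-adherent promotores, with s = 10, 20 or 30%. Adherent networks gain 23 points and non-adherent networks gain none. Follow-up response is ra = 0.8 in adherent networks and rn in non-adherent ones. Response is also 0.8 in the control phase unless stated.

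**Rollout effect.** True effect = 23 × (1 − s), that is 20.7, 18.4 and 16.1 points.

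**Model A: adherence omitted, intervention status represented.** The missing members take the mean of the observed ones, so

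estimate = 23 × (1 − s)·ra / [(1 − s)·ra + s·rn].

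For s = 0.2 and rn = 0.4: 23 × 0.64 / (0.64 + 0.08) = 20.4. For s = 0.2 and rn = 0.3: 23 × 0.64 / (0.64 + 0.06) = 21.0.

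**Model B: the listed predictors as additive cluster and time terms, without intervention status.** This was computed from expected values in a linear probability model with four clusters (10, 10, 10 and 5 promotores), five periods and no secular trend. The completed data were then analysed with cluster, time and intervention terms.

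| Missing in non-adherent networks | s | True | A | B |
|---|---|---|---|---|
| 20% (same as elsewhere) | 10% | 20.7 | 20.7 | 16.6 |
| | 20% | 18.4 | 18.4 | 14.7 |
| | 30% | 16.1 | 16.1 | 12.9 |
| 60% | 10% | 20.7 | 21.8 | 17.0 |
| | 20% | 18.4 | 20.4 | 15.5 |
| | 30% | 16.1 | 18.9 | 14.0 |
| 100% | 10% | 20.7 | 23.0 | 17.5 |
| | 20% | 18.4 | 23.0 | 16.5 |
| | 30% | 16.1 | 23.0 | 15.4 |
| 100%, none missing elsewhere | 10% | 20.7 | 23.0 | 21.8 |
| | 20% | 18.4 | 23.0 | 20.6 |
| | 30% | 16.1 | 23.0 | 19.2 |

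**Reading the table.** Under A, with 60 to 100% missing in non-adherent networks, the excess runs from 1.1 points (21.8 − 20.7) to 6.9 points (23.0 − 16.1). With equal response there is none. Under B with 20% missing elsewhere, the estimate is low by 0.7 points (15.4 against 16.1) to 3.7 points (17.0 against 20.7) in the 60% and 100% rows.

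The equal-response rows show that B's shortfall comes from leaving out intervention status. Lower response in non-adherent networks still moves B upwards: at 60% missing by 0.4, 0.8 and 1.1 points (17.0 − 16.6, 15.5 − 14.7, 14.0 − 12.9). The two omissions act in opposite directions and can partly cancel.

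**Complete-case comparison.** Under A, at 60% missing, the complete-case estimates are 21.8, 20.4 and 18.9, the same as the imputed ones, so agreement would be no evidence against bias. Under B the two would disagree (20.4 against 15.5 at s = 20%) with the truth, 18.4, between them.

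**Does adding adherence help?** A simulation used 200 replicates, 35 × 45 members, correlation 0.25, s = 0.2, rn = 0.3, and logistic imputation of intervention-phase outcomes on baseline outcome and cluster. It gave 18.4 with full data, 20.9 complete-case, 20.8 imputed without adherence and 18.2 imputed with adherence.

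**The case against.** The strongest reply is that the Missing Data section already promises sensitivity analyses under other missingness assumptions, so departures from MAR are foreseen. The predictor list is not declared exhaustive, and an article may leave auxiliary variables and the form of those analyses to the full plan. This stands in part: the section does not ignore departures from MAR. But the article itself states a cause, an assumption and a set of predictors, and these fit together poorly. Nothing ties the promised analyses to non-adherence.

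A reader might infer that the effectiveness estimate will be inflated. The documents do not support that. Upward bias needs lower response in non-adherent networks, together with either an imputation that represents intervention status or missingness concentrated in those networks. The listed predictors taken as main effects can bias downwards. There is also no bias of this kind if the programme has no effect or if non-adherent networks gain equally. In this set-up the mechanism rescales a real effect and does not create one.

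Three further cautions are fair:

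- Non-adherence is not defined in the section and could mean only that surveys were not completed.
- Pre-survey invitations are Session 2 homework, so on that schedule a promotor who stops earlier brings in no members to impute.
- The article does not state outright that the target is the effect whatever each promotor does. That is inferred from its effectiveness aim and from status following cluster crossover.

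**Conclusion.** The point holds as a mismatch between the named cause of missingness and the listed imputation predictors, with the direction of bias uncertain. Under the assumptions set out above, the error is about 1 to 7 points upward on a true effect of 16 to 21 points when the imputation reflects intervention status. It can be downward when only the listed main effects are used. All adherence and response rates, and the zero gain in non-adherent networks, are assumptions; milder differences in response give smaller errors. The complete-case comparison cannot be relied on to reveal the upward bias. The change is worth making because the variables needed are already collected and, per Trial Status, data collection is not complete.

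**What to change.** In the Missing Data section:

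1. Add the tracked promotor-level adherence measures (assignments completed, number of posts), together with intervention status, to the imputation model for intervention-phase outcomes.
2. State that all networks of a crossed-over cluster stay in the analysis as intervention, whatever their promotor's adherence.
3. Specify one of the promised sensitivity analyses as a missing-not-at-random analysis for members of non-adherent promotores' networks, either delta-adjusted or control-based. This matters most where such networks have few or no follow-up responders, because the adherence variable then has little to borrow from. Control-based imputation assumes no benefit in these members, so it belongs here and need not be the main analysis.

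The cost is a few sentences, a little more analysis work and possibly a slightly smaller or less precise estimate. No new data are needed.

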### Sample Size

The primary outcome will be vaccination-related decision-making among members of promotores’ social media networks, including willingness to receive recommended immunizations or recommend them to others.

Sample size estimates were informed by prior studies reporting vaccination coverage ranging from 33.1% to 45.4% in urban populations served by Spanish-speaking community health initiatives [33, 35]. Using these estimates, we calculated the required sample size for a paired design with a two-sided α of 0.05, 80% power, a relative risk of 1.5, and an assumed within-participant correlation coefficient of 0.25. We then applied the approach described by Hemming and Taljaard to account for the stepped-wedge cluster design, incorporating four steps, variable cluster sizes, and an intracluster correlation coefficient of 0.01 [36]. Design effect adjustments were applied to estimate overall and per-cluster sample size requirements.

Based on these calculations, we will recruit a minimum of 35 promotores across seven neighborhoods, organized into four clusters. Under the planned four-step rollout, clusters will sequentially transition from control to intervention conditions at six-month intervals. This sample size will provide 80% power to detect a meaningful difference in vaccination-related decision-making over time, corresponding to an increase from 45% at baseline to 68% during the intervention phase. To achieve adequate power, each promotor will recruit approximately 45 members of their social media network to complete baseline and follow-up surveys.

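### The listed imputation predictors omit intervention status; if cluster and calendar time enter as main effects, imputed survey outcomes dilute the primary effect roughly in proportion to missingness

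*Protocol article*

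**What the plan says.** The Missing Data section names the method: "Multiple imputation by chained equations will be used to address missing survey data under the assumption that data are missing at random". It then lists the predictors: "Imputation models will incorporate demographic variables, baseline measures, cluster indicators, and time effects". It also promises sensitivity analyses and a comparison with complete cases.

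The Surveys part of Data Analysis describes the model to be fitted: "These models will account for clustering at the promotor and neighborhood levels and will include fixed effects for time and intervention status". Time and intervention are therefore two distinct terms there.

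The imputation reaches the primary endpoint, because that endpoint comes from a survey. Sample Size states: "The primary outcome will be vaccination-related decision-making among members of promotores’ social media networks". The Surveys part of Outcomes gives the schedule: "Members of promotores’ social media networks will complete surveys at baseline, at 6-months, and post-campaign". Study Design gives the rollout: "At six-month intervals, each cluster will transition from the control condition to the intervention". No section adds intervention status, or a cluster-by-time interaction, to the imputation.

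**The concern.** An imputation model should contain every term whose effect the analysis is meant to estimate. Here the term left off the list is the intervention itself.

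Cluster and time do not stand in for it. Because clusters cross over one after another, exposure at a given survey is known only from cluster and calendar step together. Main effects of each pick up the part of exposure that is collinear with them. The stepped-wedge estimate rests on the remaining part. Values imputed from main effects alone contain none of it, so each imputed response pulls the estimate towards zero.

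This does not depend on why data are missing; it occurs under the missing-at-random assumption that the article adopts. It also undermines the planned complete-case comparison. A gap between the two analyses could be read as evidence about the missingness mechanism when the imputation model had created it.

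**Working it through.** **Inputs from the article**
- Effect (Sample Size): "corresponding to an increase from 45% at baseline to 68% during the intervention phase". A relative risk of 1.5 on 45% gives 0.45 × 1.5 = 67.5%, which agrees with the stated 68%. The difference is 68 − 45 = 23 points. The log odds ratio is ln(0.68/0.32) − ln(0.45/0.55) = 0.754 + 0.201 = 0.954 after rounding, an odds ratio of 2.60.
- Members: 35 promotores × 45 = 1,575 in four clusters.

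**Assumptions, not in the article**
- Cluster sizes. Five promotores in each of seven neighbourhoods, with three clusters of two neighbourhoods and one of a single neighbourhood, give 450/450/450/225 members.
- Missing fraction *m* of follow-up responses: 10% to 40%. Baseline is complete.
- Time in the imputation model means calendar step, entered as a main effect.

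**Why the loss is close to proportional.** In a linear model with cluster, time and intervention, the intervention coefficient is Σ n·r·y / Σ n·r², where r is what is left of intervention status after regressing it on cluster and time. Values fitted from cluster and time alone are orthogonal to r, so the imputed responses add nothing to the numerator. If the same fraction is missing in every cell, the estimate is (1 − m) × 23:
- 10%: 0.9 × 23 = 20.7
- 20%: 0.8 × 23 = 18.4
- 30%: 0.7 × 23 = 16.1
- 40%: 0.6 × 23 = 13.8

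A fully observed baseline softens this slightly.

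**Large-sample calculation.** Missing follow-up outcomes were replaced by fitted values from each candidate imputation model. The analysis model with cluster, calendar time and intervention was then fitted (five periods, baseline complete).

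| Follow-up missing | Listed predictors, points | Listed predictors, log OR | Intervention status added |
|---|---|---|---|
| 10% | about 21 | about 0.87 | 23.0; 0.954 |
| 20% | about 19 | about 0.79 | 23.0; 0.954 |
| 30% | about 17 | about 0.70 | 23.0; 0.954 |
| 40% | about 15 | about 0.61 | 23.0; 0.954 |

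On the log-odds scale the losses are about 9%, 17–18%, 26–27% and 35–36%. A three-survey layout anchored to each cluster's own start gives results within about half a point. A calendar trend of 0.05 log-odds per step changes little. Cluster-by-time terms restore the full effect just as adding intervention status does.

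**Alternative readings, by simulation.** Three surveys were tied to each cluster's own start and missingness depended on the baseline answer (60 replicates, 5 imputations, Monte Carlo error about 0.3–0.5 points). Estimates at 20% and 40% missing were:
- calendar-step main effects only: 18.7 and 14.6 points
- each wave imputed as its own variable, with cluster indicators: 22.2 and 21.9
- time taken as own survey wave: 22.1 and 22.1
- intervention status added: 22.2 and 22.0

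The loss is therefore specific to the main-effects, calendar-step reading.

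**The case against.** The strongest reply is that the article gives categories of predictor, not a full model. It does not say that the list is exhaustive, that only main effects enter, whether data are imputed in long or wide form, or that time means calendar step. With three surveys per member, imputing each wave as a separate variable is ordinary practice, and with cluster indicators it keeps the effect. Table 1 also ties the pre-survey to the cohort's own training and the post-survey to six months after its own baseline focus group, so time could mean own wave. The article condenses a fuller protocol, and imputation detail often sits in the SAP.

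Much of this stands, and it makes the bias conditional. It does not remove the point. The article chose to name the predictors, and the list lacks the one term the trial exists to estimate; an SAP that follows the sentence inherits the gap. Listing time as a predictor sits more naturally with a long-format model than with wave-by-wave imputation. If time meant own wave throughout, wave would determine intervention status, and the two separate terms in the analysis model would be collinear. Calendar step is the reading that lets Study Design and Data Analysis work together.

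The complete-case comparison might expose a discrepancy, but it would not correct the imputed estimate.

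**Conclusion.** The concern holds in conditional form. The predictor list omits intervention status, and under main effects of cluster and calendar step the primary estimate is attenuated roughly in proportion to the missing fraction: 23 points become about 21/19/17/15 at 10/20/30/40% missing. Confidence is moderate. The direction is secure under that reading. The size rests on an assumed missing fraction and assumed cluster sizes.

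Three stronger readings are tempting and not supported:
- *The primary estimate will certainly be biased.* It will not be if waves are imputed separately with cluster indicators, or if time is own wave. The text excludes neither.
- *Imputed values carry no intervention effect at all.* They lack only the part not absorbed by cluster and time.
- *Leaving out the promotor level is a demonstrated second error.* The analysis model names that level and the imputation list does not. However, the cluster indicators might be meant to include it, and no effect of the omission has been quantified.

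Nor is any figure for loss of interval coverage put forward, since the article gives no missing fraction from which to derive one.

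**What to change.** Amend the predictor sentence in Missing Data, and the SAP to match, so that the imputation models also include:
- intervention status at each survey, or cluster-by-time terms;
- the member's outcomes at the other survey waves;
- preferably the promotor level, by multilevel imputation or promotor indicators, so that imputation is compatible with the mixed model in Data Analysis.

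The same sentence should say whether time means calendar step or survey wave, and whether waves are imputed jointly in long form or as separate variables. If the team already intends wave-by-wave imputation with cluster indicators, saying so is enough to remove the attenuation.

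The cost is one sentence of wording. It needs no extra data, visits or budget, and Trial Status reports that data collection is not complete, so the change can still be made before analysis.
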